## Abstract

**Background:**

Risk-reducing salpingo-oophorectomy (RRSO) around the age of 40 is currently recommended to *BRCA1/2* mutation carriers. This procedure decreases the elevated ovarian cancer risk by 80–96 % but it initiates premature menopause as well. The latter is associated with short-term and long-term morbidity, potentially affecting quality of life (QoL). Based on recent insights into the Fallopian tube as possible site of origin of serous ovarian carcinomas, an alternative preventive strategy has been put forward: early risk-reducing salpingectomy (RRS) and delayed oophorectomy (RRO). However, efficacy and safety of this alternative strategy have to be investigated.

**Methods:**

A multicentre non-randomised trial in 11 Dutch centres for hereditary cancer will be conducted. Eligible patients are premenopausal *BRCA1/2* mutation carriers after completing childbearing without (a history of) ovarian carcinoma. Participants choose between standard RRSO at age 35–40 (*BRCA1*) or 40–45 (*BRCA2*) and the alternative strategy (RRS upon completion of childbearing and RRO at age 40–45 (*BRCA1*) or 45–50 (*BRCA2*)). Women who opt for RRS but do not want to postpone RRO beyond the currently recommended age are included as well. Primary outcome measure is menopause-related QoL. Secondary outcome measures are ovarian/breast cancer incidence, surgery-related morbidity, histopathology, cardiovascular risk factors and diseases, and cost-effectiveness. Mixed model data analysis will be performed.

**Discussion:**

The exact role of the Fallopian tube in ovarian carcinogenesis is still unclear. It is not expected that further fundamental research will elucidate this role in the near future. Therefore, this clinical trial is essential to investigate RRS with delayed RRO as alternative risk-reducing strategy in order to improve QoL.

**Trial registration:**

ClinicalTrials.gov (NCT02321228)

## Background

### BRCA germline mutations and ovarian cancer

Epithelial ovarian cancer is the most lethal malignancy of the female genital tract. With respect to treatment and prognosis, primary carcinomas of the ovaries, fallopian tubes and peritoneum are considered one disease entity often referred to as ‘ovarian carcinoma’. Women with germline mutations in one of the two *BRCA* genes are at increased risk of developing breast and ovarian cancer. Cumulative breast cancer risks are estimated 57–65 % (95 % CIs: 44–78 %) for *BRCA1* and 45–49 % (95 % CIs: 31–57 %) for *BRCA2* mutation carriers by age 70, whereas cumulative ovarian cancer risks lie around 39–40 % (95 % CIs: 18–54 %) and 11–18 % (95 % CIs: 2.4–23 %) by the age of 70 for *BRCA1* en *BRCA2*, respectively [1, 2]. Ovarian carcinoma occurs at younger age in *BRCA1* mutation carriers than in *BRCA2* mutation carriers or the general population (both mean and median 51 versus 56 versus 60 years respectively) [3]. In *BRCA1/2* germline mutation carriers, approximately 65 % of all ovarian carcinomas are of the serous subtype [4–6].

### Risk-reducing salpingo-oophorectomy (RRSO)

In contrast to breast cancer surveillance, screening for ovarian cancer has been highly ineffective [7–9]. Therefore, the only intervention to reduce ovarian cancer risk is risk-reducing salpingo-oophorectomy (RRSO), which decreases ovarian cancer incidence by about 80–96 % [4, 10–12]. However, this effect might be underestimated due to studies that included women who underwent oophorectomy alone and/or underwent surgery above the currently recommended age: 35–40 for *BRCA1* and 40–45 for *BRCA2* mutation carriers [4, 11, 13]. The residual risk of primary peritoneal cancer after RRSO is approximately 1 %; however, it was also reported to be more than 4 % [10, 14–16]. RRSO is often laparoscopically performed at an outpatients’ department. Serious surgical complications rates are low [4, 17, 18]. Main adverse effects of RRSO are related to premature surgical menopause, including short-term effects like vasomotor symptoms (i.e. hot flushes), sleep disturbances, vaginal dryness and sexual symptoms [4]. Long-term effects include osteoporosis, increased risk of cardiovascular disease, cognitive impairment and increased depressive and anxiety symptoms, although prospective studies on these long-term effects in *BRCA* mutation carriers in particular are not available [4, 19–22]. Postsurgical hormone replacement therapy (HRT) does not fully alleviate climacteric and sexual symptoms [20, 23]. The reduction of breast cancer incidence by half achieved by performing RRSO at premenopausal age [11, 12] has recently become arguable [24–26] and therefore questionable as motivation to undergo RRSO.

### Role of Fallopian tube in “ovarian” carcinogenesis

Based on recent scientific insights, the Fallopian tube is considered the most important site of origin of pelvic high grade serous carcinoma nowadays [27–31]. It is suggested that benign tubal epithelium can transform into serous tubal intraepithelial carcinoma (STIC) or invasive tubal carcinoma [32]. The (pre)malignant cells can exfoliate from the tubal epithelial lining and migrate to the ovary and abdominal cavity. This theory is based on several findings. First, no clear precursor of ovarian cancer has been found in the ovary itself. Second, earlier studies showed the presence of STIC in 36–60 % of sporadic pelvic serous carcinomas [33–35] which harboured identical mutation in the TP53 gene to the cells of concurrent pelvic serous carcinomas in 92 % [36]. Third, pelvic serous carcinoma cells resemble tubal lining epithelium more than ovarian surface epithelium [37]. Several investigators focused on prophylactically removed Fallopian tubes of germline *BRCA1/2* mutation carriers, showing the presence of STIC in about 4 % (range 0–12 %) [14, 38–47]; nearly all STICs were localised in the tubal distal fimbrial ends [34].

### Innovative preventive strategy: risk-reducing salpingectomy (RRS) with delayed oophorectomy (RRO)

The growing evidence of the role of the Fallopian tube in the origin of serous ovarian carcinoma together with the disadvantages of premature surgical menopause caused by RRSO, underlie the need for an alternative risk-reducing strategy. RRS upon completion of childbearing offers an early, potentially risk-reducing intervention; however, it is still uncertain whether and to what extent the risk of ovarian cancer will be reduced. Furthermore, around 68 % of occult carcinomas are found in tubes [48] and could now be detected at an early stage. The main advantage of delaying subsequent RRO beyond the currently recommended age will be postponement of premature menopause and its effect on noncancer-related morbidity and (menopause-related) quality of life (QoL). Several authors previously suggested this innovative strategy [48–50] and a feasibility study among both professionals and germline *BRCA1/2* mutation carriers from our group showed a broad national support to evaluate this new strategy in a prospective study [51].

### Objective

The aim of this study is to determine whether an innovative risk-reducing strategy, consisting of RRS upon completion of childbearing with delayed RRO, results in better menopause-related QoL without increase of ovarian and breast cancer risk in germline *BRCA1/2* mutation carriers compared to standard treatment, consisting of RRSO at currently recommended age.

## Methods/Design

### Study design

We will perform a nationwide prospective non-randomised multicentre trial in 11 hospitals with a department for hereditary cancer. Eligible patients will have the opportunity to choose for standard or innovative strategy. Women who opt for RRS but do not want to postpone RRO beyond the currently recommended age or are unsure about this at enrolment are included as well; however, they will not contribute to the number of inclusions needed according to the sample size calculation. See Fig. 1 for an overview of the study design.

**Fig. 1 Fig1:**
[figure not shown]
TUBA study design

Although a randomised controlled trial would be the preferred study design, an earlier published feasibility study among healthcare professionals and germline *BRCA1/2* mutation carriers showed that randomisation would be an insurmountable barrier for participation in a clinical study [51]. These women want to decide themselves on their risk-reducing strategy and it is therefore unlikely that they will participate in a randomised controlled trial. Taken this into account, a prospective non-randomised design seems the most appropriate, letting women the opportunity to decide for themselves.

In addition, a control group will be formed by women who underwent RRSO between 1 and 5 years ago, in order to compare QoL between study participants and women who did not have the opportunity to choose for an alternative treatment.

### Study population

HospitalsEleven hospitals with a hereditary cancer department will participate in this study, of which seven are university tertiary hospitals.PatientsWomen carrying a documented germline *BRCA1/2* mutation from the department of Clinical Genetics or Hereditary Cancer of each hospital, who are between 25 and 40 (*BRCA1*) or 45 (*BRCA2*) years old without previous RRSO.Inclusion criteriaPremenopausal women with a documented *BRCA1* and/or *BRCA2* gene germline mutationAge 25–40 years for *BRCA1* mutation carriers and 25–45 years for *BRCA2*Childbearing completedPresence of at least one Fallopian tubeParticipants may have a personal history of non-ovarian malignancyInformed consentExclusion criteriaPostmenopausal status (natural menopause or due to (cancer) treatment)Wish for second stage RRO within two years after RRS (if clear at enrolment)Legally incapablePrior bilateral salpingectomyA personal history of ovarian, Fallopian tube or peritoneal cancerEvidence of malignant disease at enrolmentCurrent treatment for malignant diseaseInability to read or speak DutchPatient recruitmentEligible women will be sent a letter to inform them on this study. *BRCA1/2* mutation carriers will be asked to respond whether or not they would be interested to participate. If they are interested, the patient information form will be sent and an appointment will be made to explain the rationale, design and aims of the study in person. The patient will have sufficient time (minimal one week) to consider the study before deciding to participate. Written informed consent from the patient is required before participation.

Furthermore, every newly diagnosed germline *BRCA1/2* mutation carrier at the department of Clinical Genetics that fulfills the inclusion criteria will be informed on the study.

### Outcome measures

Primary outcome measureMenopause-specific QoL, measured by the Greene Climacteric Scale (GCS) questionnaire in Dutch [52]. This questionnaire consists of 21 items divided into various domains: psychological (11 items, divided into anxiety and depression subscales), somatic (7 items), vasomotor symptoms (2 items) and sexual (1 item). Each symptom is rated according to its severity using a four-point Likert scale. The Greene Climacteric score is the sum of all 21 items ranging from 0 to 63. A higher total score corresponds with more menopausal symptoms.Secondary outcome measuresGeneral QoL and QoL-related items, measured by several questionnaires (see section Pre-treatment evaluation)Incidence of ovarian and breast cancerSurgical complications, e.g. infection, conversion, haemorrhage and complications at the second laparoscopic procedure (RRO) due to previous RRS.Histopathological findings of removed Fallopian tubes and ovaries, i.e. (pre)malignanciesCardiovascular risk factors and incidence of cardiovascular diseaseCost-effectiveness of the innovative treatment compared to standard treatment

### Interventions

Standard treatment (control arm):

RRSO between age 35–40 in *BRCA1* mutation carriers and between 40–45 in *BRCA2* mutation carriers (exact ages varying across different hospitals) and when childbearing is completed.

Innovative treatment (experimental arm):

RRS when childbearing is completed with second stage RRO delayed for five years compared to the currently recommended age for RRSO, i.e. at the age of 40–45 in *BRCA1* and 45–50 in *BRCA2* mutation carriers. Regarding the definitive contraception which is a result of RRS and the age at which RRS is performed, women will be counseled in a similar manner as women consulting the gynaecologist for sterilization. RRS will be performed according to Leblanc et al*.* [53]. Whenever a (pre)malignancy is found in the RRS specimen, RRO will be performed as soon as possible, as well as additional surgery or treatment if necessary, e.g. staging procedure.

### Data collection

Pre-treatment evaluationAll patients will be asked to fill out web-based baseline questionnaires. Questionnaires on demographic data and medical history with a special focus on cancer and cardiovascular risk factors are included. Furthermore, QoL(−related) questionnaires include Dutch versions of the Greene Climacteric Scale (GCS) [52], SF-36 [54], EQ-5D-5 L [55], Cancer Worry Scale (CWS) [56, 57], Female Sexual Function Index (FSFI) [58, 59], Female Sexual Distress Scale (FSDS) [59, 60] and Decisional Conflict Scale (DCS) [61]. Questions based on the Institute of Medical Technology Assessment Productivity Cost Questionnaire (iPCQ) [62] and the Medical Consumption Questionnaire (iMCQ) [63] will be used to collect data on productivity loss and health consumption. Moreover, blood pressure, body mass index and waist-hip ratio will be documented. Fasting blood samples will be taken to measure cardiovascular risk factors.Follow-upSix weeks after surgery, data on surgical complications and histopathological findings are collected. The *Sectioning and Extensively Examining the FIMbriated End (SEE-FIM) of the Fallopian Tube* (SEE-FIM) protocol will be used for the latter [64]. Follow-up by web-based questionnaires as described at baseline except for the Decisional Conflict Scale is scheduled at 3 and 12 months after surgery. At 1, 5 and 15 years follow-up, the Decision Regret Scale (DRS) is added [65]. From one year after surgery, questionnaires will be sent biennially until the end of follow-up (in case of only one surgery in the standard treatment arm) or until undergoing RRO (in the innovative arm). After RRO, data will be collected at six weeks and 3 and 12 months after surgery, comparable to follow-up after the first operation, and then biennial questionnaires will be sent until the end of follow-up, 15 years after the last (or only) surgery. Additionally, blood pressure, body mass index, waist-hip ratio and cardiovascular risk factors in fasting blood samples will be collected five years after each surgery. Follow-up by questionnaires will continue biennially until 15 years after the last surgery to detect occurrence of ovarian cancer. Since the wide possible range of age at inclusion, timing of surgeries and interval between surgeries, it is hard to specify and generalize the exact amount and timing of follow-up. A flowchart visualising the follow-up schedule can be found in Fig. 2.

**Fig. 2 Fig2:**
[figure not shown]
Schedule of follow-up in TUBA studyCost-effectivenessThis economic evaluation will compare costs and quality adjusted life years (QALY) of the innovative treatment with standard treatment. The perspective of this economic evaluation will be a societal perspective. Both healthcare and societal costs which can be related to this study will be assessed until 15 years after last surgery. Costs are collected on a per patient level. The incremental costs of innovative care compared to standard care will be based on the difference in costs between groups. The healthcare costs, measured by the Medical Consumption Questionnaire (iMCQ) tailored to this context, will be calculated. Societal costs will be calculated from a selection of the Productivity Cost Questionnaire (iPCQ). The output or consequences of both innovative and standard care will be determined by measuring QoL before and during the study. The SF-36 and EQ-5D-5 L will be used for this analysis. The outcomes will be translated to a long-time difference in QALY. Key variables will be varied in a sensitivity analysis to evaluate their impact on the incremental costs per QALY gained ratio. Including the innovative strategy in future guideline recommendations depends on the incremental cost per QALY. As mentioned before, data will be collected until 15 years after last surgery. However, an interim cost-effectiveness analysis will be performed after eight years to provide information for proceeding implementation. Recommendation for implementation will be based on the empirical cost data completed with modelled costs over the remaining period. Accuracy of this model will be evaluated at the end of 15 years follow-up, when data collection on the actual costs during the remaining seven years will have been completed.Potential adverse eventsIn the innovative treatment, *BRCA1/2* mutation carriers will undergo an additional laparoscopy. Known complication rates for RRSO in a comparable population vary from 0.6–5 % for major complications (conversion, bladder or bowel injury, additional surgery required) and 3.7–10 % for minor complications (infection, bleeding, haematoma) [17, 18, 42, 66]. Risks might be lower for RRS alone. As mentioned before, data on surgery-related complications will be collected six weeks after each surgery.

Furthermore, the worst-case scenario is that RRS does not reduce ovarian cancer risk at all. Then, the postponement of RRO for five years might result in a higher ovarian cancer incidence in the experimental arm. We used a model to calculate the risk for interval ovarian carcinoma when RRO is performed five years later than the current guideline age. The risk to develop ovarian carcinoma within these five years is estimated to be up to 1–2 % for *BRCA1* mutation carriers and up to 0.5–1 % for *BRCA2* mutation carriers. Cancer incidence will be monitored by questionnaires.

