### Statistical analysis

Sample size calculationThe primary outcome measure is menopause-specific QoL. Menopausal symptoms will be assessed by the Greene Climacteric Scale (GCS). The main comparison is the difference in GCS between women getting the innovative treatment and women getting standard RRSO without postsurgical hormone replacement therapy (HRT), which is about one third of women after RRSO.This difference is estimated at five points on the GCS, with standard deviation 7.36, based on figures of Barentsen et al. [67]. Each hospital will provide both innovative and standard treatment, based on patient choice (no randomization). We assume an intra-cluster correlation coefficient ≤ 0.10. When we have about 10 hospitals, with 51 patients per hospital (total *n* = 510), we expect that the majority of hospitals (7 hospitals or more) will provide at least 3 patients with the innovative treatment. The remaining hospitals (3 or less) provide 51 patients with standard treatment of whom 16 will be on RRSO without HRT. This scenario gives an 80 % power (alpha = 0.05).Data analysisTo test differences between two subgroups on the course of QoL since baseline, we will carry out a mixed model analysis to accommodate for hospital effects and repeated measurements. All secondary outcome measures will be analysed using mixed models in a similar manner. Cost-effectiveness, as far as it concerns the empirical data, is analyzed in a stochastic fashion using bootstrapped regression based techniques (i.e., linear mixed model) adhering to the net benefit framework.SafetyAn independent Data Safety Monitoring Board (DSMB) is established, existing of three independent experts who have no conflict of interest. This committee will meet once a year to perform interim analysis specifically with respect to safety. The DSMB will report to the study coordinator and may recommend changes in the conduct of the study or even premature study termination.

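### Cancers presenting clinically between or after the operations are traced only through the women's own questionnaires, so cases can be lost and those reported reach the yearly DSMB review late

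*Protocol article*

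**What the plan says.** The Objective seeks better menopause-related quality of life "without increase of ovarian and breast cancer risk", and incidence of ovarian and breast cancer is a secondary outcome. Under Potential adverse events, the article considers the worst case, in which salpingectomy gives no protection and oophorectomy comes five years later. It then states how cancer is followed: "Cancer incidence will be monitored by questionnaires".

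Data collection (Follow-up) gives the timetable. Web-based follow-up "is scheduled at 3 and 12 months after surgery", and then: "From one year after surgery, questionnaires will be sent biennially until the end of follow-up" or, in the innovative arm, until oophorectomy, after which the cycle restarts. The long-term purpose is explicit: "Follow-up by questionnaires will continue biennially until 15 years after the last surgery to detect occurrence of ovarian cancer". The same section collects histopathology of the removed tissue six weeks after surgery, and cardiovascular measurements five years after each operation.

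On oversight, the Safety paragraph of Statistical analysis says of the DSMB: "This committee will meet once a year to perform interim analysis specifically with respect to safety". The Discussion adds that follow-up is extended beyond the quality-of-life data so that cancer incidence is watched closely.

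**The concern.** Ovarian cancer during the years of delayed oophorectomy is the hazard that the article itself identifies, and few cases are expected. The route named for finding a clinically presenting case is a web form that the woman completes herself. A woman who has died cannot complete it, and a seriously ill woman is less likely to. The Background calls epithelial ovarian cancer the most lethal cancer of the female genital tract, so non-response may well be related to the outcome. Follow-up runs to 15 years after the last operation, which gives ordinary non-response time to build up. No second source is named for deaths or non-responders.

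Timing is the other difficulty. The DSMB reviews safety every year, but after year 1 each woman is asked only every second year. At stake are the completeness of a small case count and the speed with which a signal reaches the people who can act on it.

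**Working it through.** The article's five-year risks come from a model whose inputs are not given, so they cannot be reproduced and are taken as stated.

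**1. Which cancers depend on self-report**

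| Cancer | Source named in the article |
|---|---|
| Found in a removed tube or ovary | Histopathology, six weeks after each operation |
| Presenting clinically in the first year after an operation | Questionnaires at 3 and 12 months |
| Presenting clinically later, before or after the last operation | Questionnaire every two years |

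The second and third rows rest on questionnaires. The third covers most of the interval between salpingectomy and delayed oophorectomy, and nearly all the time after the last operation.

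**2. Reporting delay after year 1**

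Inputs: questionnaire interval 24 months and DSMB interval 12 months, both from the article. Assumptions: diagnosis falls at random within the questionnaire interval, the next form is returned, and the DSMB hears of the case only through it.

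- Mean delay from diagnosis to report = 24 / 2 = 12 months; maximum 24, or 24 + 24 = 48 if one form is skipped.
- Share of cases waiting more than 12 months = (24 − 12) / 24 = 50%.
- Mean delay from diagnosis to the next DSMB meeting after the report = 12 + 12 / 2 = 18 months.
- Share of cases not in hand at the first DSMB meeting after diagnosis: if that meeting falls at a time N, uniform on 0 to 12 months, the chance that the form comes later is 1 − N/24, which averages 1 − 6/24 = 75%.

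A simulation of one million draws gave the same values (12.0 months, 50%, 18.0 months, 75%).

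**3. How many interval cancers are at issue**

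Stated worst-case five-year risks: "The risk to develop ovarian carcinoma within these five years is estimated to be up to 1–2 % for" *BRCA1* carriers "and up to 0.5–1 % for" *BRCA2* carriers. The planned total is 510. The split follows patient choice and is not fixed; 255, half of the total, is an assumption.

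Expected cases = number of women × risk:

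- 255, all *BRCA2*: 255 × 0.005 = 1.3 to 255 × 0.01 = 2.6.
- 255, all *BRCA1*: 255 × 0.01 = 2.6 to 255 × 0.02 = 5.1.
- Any mix of the two lies between 1.3 and 5.1.
- With 100 women the full range is 0.5 to 2.0; with all 510 it is 2.6 to 10.2.

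For 255 women, one lost case would be between 1 / 5.1 = 20% and 1 / 1.275 = 78% of the expected number. Some interval cancers would be found in the oophorectomy specimen and so are not exposed to this loss.

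**4. The share missed**

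The article gives no response rate and no survival figure. Purely for illustration, if 10 to 30% of all interval cases went unreported (assumption), 5.1 expected cases would become 4.6 to 3.6, and 2.55 would become 2.3 to 1.8. This shows scale only; it is not an estimate.

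**The case against.** The strongest reply is that this is a condensed article. Registry linkage, chasing of non-responders, notification of deaths and expedited reporting to the DSMB often stand in the full protocol, and their absence here does not show that none is planned. The figure with the follow-up schedule is also not available. That stands as a caution, and it limits the DSMB point: the article does not say what data the DSMB receives. It does not remove the main point, because the article states the method outright in two places. If linkage exists, those two statements describe the method wrongly and should be corrected.

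A reader might also infer stronger things that the document does not support:

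- *Questionnaires are the only source for any cancer.* They are not; specimen pathology is collected after every operation.
- *Women in the standard arm have no further contact.* They have questionnaires at 3 and 12 months and every two years, and a measurement contact five years after surgery.
- *Linkage would remove unequal detection between arms.* It would not. Occult cancer found at oophorectomy follows from having a second operation, and a registry would still record it in the innovative arm only. That extra detection counts against the innovative strategy.
- *Cases are certain to be missed.* A woman may report a diagnosis before she dies or stops responding.

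Finally, cancer is a secondary outcome and the sample size rests on the Greene scale. With so few events, a comparison between arms would be weak even with complete data. That is true. It tempers any claim that one case would settle the safety question, but it is no reason to accept avoidable loss in a small count.

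**Conclusion.** The concern holds for cancers that present clinically between or after operations. For these the article names only self-report, every two years after year 1. Followed as written, this can lose cases in women who die or stop responding, and it delays reports by 12 months on average and by up to 24, or 48 with one skipped form. Both fit poorly with the aim of no increase in cancer risk and with the close watch promised in the Discussion.

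The figure of 1.3 to 5.1 interval cancers rests on an assumed 255 women in the innovative arm and on the article's worst-case risks, which are upper figures. The delay rests on diagnosis at random times and on returned forms; the DSMB timings also assume that questionnaires are its only feed. The number of cases that would be missed cannot be derived from the document, and no particular degree of undercounting should be claimed. This is a worthwhile and inexpensive improvement, and it does not affect the primary analysis.

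**What to change.** In Data collection (Follow-up) and Potential adverse events, name linkage as the primary source for cancer: a cancer or pathology registry, or the records of the participating hospitals, together with vital status and cause of death. Apply it to ovarian, tubal, peritoneal and breast cancer in every enrolled woman, including those who no longer respond. Refresh it before each yearly DSMB meeting and keep the questionnaires as a secondary source. In the Safety paragraph, state how a newly known case reaches the DSMB between questionnaires. If the full protocol already provides this, correct the two statements in the article to match.

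The cost is a linkage clause in the consent form, an addendum for women already enrolled, and a yearly data request. No extra visits or procedures are needed.
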